### Data and power analysis

The analyses will include a quantitative assessment of Aims 1 to 3 and an economic cost analysis. Table 1 outlines the study aims and hypotheses. The data and power analysis approaches are presented in sequence for each aim by hypothesis for the experimental comparison only, as the pooled-group analyses have inferential limitations. Power was assessed using SamplePower 3.0 [73].

#### Specific aim 1

For hypothesis 1, the program is the unit of analysis, and DDCAT (fidelity) scores represent the dependent variable and the cohort assignment (NIATx vs. wait-list) is the independent variable. A two tailed analysis of covariance (α = 0.05) with 25 programs per cohort group will compare post- implementation mean fidelity scores between groups, with pre-implementation scores as the covariate. With a correlation between pre- and post- implementation DDCAT scores equal to 0.5, this analysis has power (β = .86) to detect a large effect. Prior research concerning one-year changes in DDCAT scores suggests that we can expect a large effect [62].

#### Specific aim 2

The date of the DDCAT assessment will serve as the index date for hypothesis 2 (Aim 2). All patients admitted to each program, 45 days before and 45 days after the DDCAT assessment date, will be extracted from the state administrative databases. The outcomes will be the proportion of program patients: 1) screened, 2) diagnosed, and 3) receiving integrated medication and psychosocial services, compared to ad hoc strategies (wait-list comparison sites). Each outcome has a value of 1 (yes) or 0 (no), and interest is in the difference in the rate of each outcome, accounting for the clustering of observations within sites. This analysis calls for a multi-level logistic regression model. The observations at each time point are independent, and therefore this is not a longitudinal (repeated measures) analysis. Instead, there are four independent groups (NIATx pre-implementation, NIATx post-implementation, wait-list pre-implementation, and wait-list post-implementation) in a 2 (group) by 2 (time) analysis, with primary interest in the group by time interaction. Due to the large number of observations, a logistic regression has power equal to 0.75 to detect a small effect (OR = 1.5; .10 difference in proportions) and power of 1.0 to detect a medium effect (OR = 2.33; .20 difference in proportions). These power estimates are based on standard logistic regression. We will apply a correction to the standard errors to adjust for the interclass correlation at the site level in order to avoid Type I errors due to the dependence of the clustered observations [74].

#### Specific aim 3

Aim 3 will evaluate variation in the extent of, and fidelity to, NIATx strategies. The specific hypothesis is that programs with more facilitating factors, evaluated using the CFIR Index dimensions, will be more likely to complete the NIATx protocol and to do so with greater participation and fidelity. The programs are the unit of analysis, and the primary predictor variable is the number of factors that support implementation. There are two dependent variables, a continuous variable indicating the proportion (%) of the 22 NIATx tasks completed (SIC) and a continuous variable indicating the degree of fidelity to the NIATx protocol (1 to 5-point scale). Multiple regression analyses will be used to evaluate both outcome variables. Characteristics of the sites that are associated with the outcomes will be added as covariates in the regression models in order to evaluate the effect of the CFIR Index dimensions (e.g., Perceptions of the System and Community Score) after controlling for other predictors. Power for the two-tailed multiple regression analysis (α = 0.05) across 50 programs, and 5% of the variance explained by the covariates, is 79% power to detect a change in R^2^ of 15 and 82% power to detect a change in R^2^ of 16%, when adding the primary predictor to the model.

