### NIATx implementation strategy

Programs in the NIATx intervention will be assigned a NIATx trained process improvement coach who leads the active implementation phase. Over a 12-month active implementation period, the coach works with executive directors, change leaders and teams. Coaching includes a one-day site visit and individual monthly phone conferences (10 h total) with each program.

Prior to the site visit, the coach will introduce the project, review initial DDCAT results, discuss how to conduct a walk-through [64] and set the stage for the site visit. The site visit will use a standardized agenda to ensure fidelity. During the visit, the coach will meet with executive leadership, review the walk-through and DDCAT assessment results, and train staff on the use of the NIATx implementation strategies. With their coach, the program will utilize results from the DDCAT assessment to identify areas for improvement, implement change projects and assess their impact.

After the site visit, the coach will conduct bi-monthly coaching calls with their assigned programs for the 1st quarter of the implementation period and monthly calls thereafter. In the individual calls, the coach and change team will review change projects, discuss successes, and identify new change projects. In addition to individual coaching calls, the coach provides support through learning sessions and group coaching calls.

Two group calls, moderated by the coach, will involve change leaders from multiple programs and provide an opportunity for peer-to-peer sharing. On these calls, the change leaders will discuss common change-related issues, progress, and exchange innovative implementation strategies with their peers. The calls will also allow the coach to share new strategies and discuss implementation issues such as sustainment of organizational change.

The study will include two one-day coach-led learning sessions for all programs within a cohort. Learning sessions promote peer-to-peer sharing about specific goals and objectives using a tailored agenda. The first learning session will teach programs how to use NIATx process improvement strategies through skill development activities such as how to identify change opportunities, develop PDSA cycles and effective use of data to drive change. The second learning session will include program presentations about change efforts and discuss how to develop sustainment plans to continue to improve integrated services.

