### Randomization

The randomization sequence will be generated by the study biostatistician and concealed from the researchers conducting study assessments. An equal number of programs will be randomized to each study arm. However, the coaches will not be blinded to the results of randomization as they will be assigned to programs in Cohort 1 after the baseline DDCAT assessment is completed. After the baseline DDCAT assessment is completed, the program along with their coach, will be notified of their intervention assignment (Cohort 1) or the program will be notified that they have been assigned to the wait-list control group (Cohort 2).

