3	NIATx Fidelity Scale^3^	NIATx strategy fidelity and extent of and duration to complete activities (SIC)		X		
1	Program characteristics^1^	Program Size (Admissions), Program Type, ASAM Levels of Care, Payment Sources	X	X	X	X
2	Patient Characteristics	Age, Gender, Race, Ethnicity	X	X	X	X

State of Washington staff will be trained on how to conduct DDCAT and CFIR Index assessments by co-PI ([name]). Two-person teams will schedule and conduct each DDCAT assessment. Additional training or consultation will help answer questions identified at the site visits. Program characteristics are collected during the DDCAT assessments

Data will be collected by the state of Washington staff and NIATx coaches using standardized instruments for each program participating in the study

NIATx Fidelity scoring (Total and 7 subscale scores are organized by preparation, implementation and sustainment phases) will be assessed by two person teams at the end of the active implementation period for each program. Data sources will include a composite of interviews, review of walk-through results, change project forms, coach notes and sustainability plans

At the time of the study, Washington State was transitioning to Managed Care Organizations (MCOs) to pay for the delivery of substance use disorder (SUD) and mental health (MH) services. The transition involved integrating data from two systems: 1) the Treatment and Assessment Reports Generation Tool (TARGET), covering SUD clients and services; and 2) the Mental Health Consumer Information System (MH-CIS), covering community MH clients and services into a new Behavioral Health Data System (BHDS). The study will capitalize and leverage the State of Washington’s experience in utilizing standardized state-wide clinical management information databases for addiction and mental health treatment [67–70]. Implementation penetration outcomes will assess changes in the proportion of patients screened, diagnosed and receiving integrated psychosocial or medication services (Aim 2). The services data will be extracted from the BHDS as well as TARGET and MH-CIS legacy systems. It will include de-identified client level data for all patient admissions to study programs within a 45-day window before and after each DDCAT assessment date (Additional file 1). The information will be transferred to the study team using appropriate security protocols.

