The CFIR Index operationalized four CFIR dimensions (Characteristics of the Intervention; Outer Setting, Inner Setting, Characteristics of Individuals) to create an objective rating scale to evaluate pre-implementation factors as moderators of the implementation process over time, and as factors in sustainability (Aim 3). The index has good preliminary psychometric properties [71, 72]. Summary ratings from the CFIR Index dimensions may predict fidelity to and extent of completion of the NIATx strategies (Aim 3). Data collection for the CFIR Index will follow the same schedule as the DDCAT assessment.

Fidelity to and participation in the NIATx implementation strategies will be assessed using two exploratory scales specifically developed for this study: NIATx Fidelity Scale, and the NIATx Stages of Implementation Completion (NIATx SIC). The NIATx Fidelity Scale includes 19-items designed to assess adherence to the NIATx model on a 5-point scale from 1- No evidence to 5-Extensive evidence. The NIATx SIC is based on a modified version of the SIC and is organized into three phases: Pre-implementation, Implementation and Sustainment (Table 3). Program driven activities will be scored and count toward both duration (number of days) and proportion (number of scored activities completed/total number of scored activities possible) within a given phase of the NIATx SIC. The use of these scales will be utilized to assess variation in the extent and fidelity to which NIATx strategies are delivered.

**Table 3 Tab3:** Overview of the NIATx Stages of Implementation Checklist

NIATx SIC Phases and Stages in Each Phase	# of Items	Examples of NIATx SIC Elements
Program Characteristics	17	Program Size, Type, Primary Focus
Pre-Implementation Phase Stage 1: Engagement	6	Invite Date, Contacts before Accept
Pre-Implementation Phase Stage 2: Consideration of Feasibility	8	DDCAT Assessment Date, Contacts
Pre-Implementation Phase Stage 3: Readiness Planning	18	Initial Coach Engagement & NIATx Webinar, Change Leader Appointed
Implementation Phase Stage 4: Staff Hired and Intro Training	5	Change Team Identified, Coach Site Visit
Implementation Phase Stage 5: Fidelity Monitoring & Tracking in Place	4	Review of Walkthrough, Project Selection
Implementation Phase Stage 6: Services & Consultation to Services Begin	4	Collect baseline data, Start Change Project

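### The Aim 2 admission window can carry post-notification admissions into the Cohort 1 baseline and, if wait-list programs start promptly, NIATx-exposed admissions into the control follow-up

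*Protocol article*

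**What the plan says.** All references are to the protocol article.

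- **Data and power analysis, Specific aim 2:** the DDCAT date is the index date, and the extract covers "All patients admitted to each program, 45 days before and 45 days after the DDCAT assessment date". The four cells are NIATx and wait-list, each pre- and post-implementation. Primary interest is in the group-by-time interaction.
- **Data collection/variables:** the same rule applies at every assessment, "within a 45-day window before and after each DDCAT assessment date".
- **Randomization:** of the coaches it says "they will be assigned to programs in Cohort 1 after the baseline DDCAT assessment is completed". Programs in both cohorts are told their allocation at that same point.
- **NIATx implementation strategy (under Methods):** "Prior to the site visit, the coach will introduce the project, review initial DDCAT results, discuss how to conduct a walk-through". The site visit, change projects and a 12-month active period follow.
- **Table 3:** the DDCAT date sits in Stage 2. Stage 3, readiness planning, gives as examples "Initial Coach Engagement & NIATx Webinar, Change Leader Appointed". The start of a change project appears only in Stage 6.

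The text gives no number of days from the baseline DDCAT to notification, coach contact, site visit or first change project. It gives none from the wait-list follow-up DDCAT to the Cohort 2 start. The design and timeline figures are not shown.

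**The concern.** Holding back the allocation until the baseline DDCAT is complete protects the Aim 1 baseline. The two-sided window gives up that protection for Aim 2, because up to half of the baseline cell can be admitted after Cohort 1 knows its allocation and has a coach. The cost analysis in the same article separates its periods at randomization; Aim 2 has no comparable cut.

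The direction of the bias is predictable. An early benefit raises the Cohort 1 baseline. If the wait-list starts soon after its follow-up DDCAT, an early benefit raises the control follow-up as well. Both shrink the interaction. The planned standard-error correction for clustering changes the precision and leaves this bias in place. The stated power for the small effect is 0.75, from a calculation that ignores clustering, so there is little to spare.

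**Working it through.** **The plan's own figure.** Aim 2 power is stated as 0.75 at OR 1.5 (difference 0.10) and 1.0 at OR 2.33 (difference 0.20). No patient number is given, so the figure can only be solved backward. Assumptions: two-sided alpha 0.05 (stated for Aim 1), reference proportion 0.50 (0.50 against 0.60 gives OR 1.5; 0.50 against 0.70 gives 2.33), equal cells, no clustering.

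- Interaction test: SE = √Σ[1/(n·p(1−p))] over four cells; power = Φ(log OR/SE − 1.96).
- With n = 683 per cell: SE = √[(4 + 4 + 4 + 4.167)/683] = 0.154. Then 0.4055/0.1539 = 2.635, and Φ(0.675) = 0.75.
- At OR 2.33 the same n gives 0.9997. A plain two-group test needs 343 per group and also gives 0.75 and 0.9997. The two stated powers therefore agree with each other.

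**Dilution.** Let f1 be the exposed share of the Cohort 1 baseline window, f2 the exposed share of the wait-list follow-up window (each at most 45/90 = 0.5), and g the share of the full effect already reached in those admissions. Then

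interaction = 0.10 × [1 − g(f1 + f2)].

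None of f1, f2 or g is in the documents, so the results are a range (683 per cell):

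| Scenario | Interaction | OR | Power |
|---|---|---|---|
| No overlap | 0.100 | 1.50 | 0.75 |
| g = 0.25, baseline end only (f1 = 0.5) | 0.0875 | 1.43 | 0.64 |
| g = 0.25, both ends | 0.075 | 1.36 | 0.51 |
| g = 1, baseline end only | 0.05 | 1.23 | 0.26 |
| g = 1, both ends | 0 | 1.00 | 0.03 |

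The g = 1 rows are a ceiling: they need the full effect from the first day of a 12-month programme.

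**Gradual build-up.** Suppose the effect grows linearly over 365 days from the DDCAT date and the follow-up DDCAT falls at day 365.

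- Mean effect share in a contaminated window: 0.5 × (22.5/365) = 0.031.
- Mean effect share in the Cohort 1 follow-up window: 0.5 × (1 − 22.5/365) + 0.5 = 0.969.
- No overlap: 0.10 × 0.969 = 0.097, OR 1.48, power 0.72.
- Baseline end only: 0.10 × (0.969 − 0.031) = 0.094, power 0.70.
- Both ends: 0.10 × (0.969 − 0.062) = 0.091, OR 1.45, power 0.67.
- Both ends with a 30-day lag: mean share (15/90) × (7.5/365) = 0.003, interaction 0.096, power 0.72.
- Lag of 45 days or more: no loss.

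**Choice of remedy under the same build-up.** Moving every window to the 90 days ending on the DDCAT date pulls the Cohort 1 follow-up into active implementation: mean share 1 − 45/365 = 0.877, interaction 0.088, power 0.64. That is below the planned window. A 45-day window ending on the DDCAT date in all cells gives 0.094 but halves n, and power is 0.42. Moving only the baseline window gives 0.094 and power 0.70 even if the wait-list follow-up is still contaminated.

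**The case against.** Notification is not changed care. Table 3 places readiness planning, the change team and site visit, walk-through review and project selection between the DDCAT and a started change project. Admissions in those weeks may have met usual practice. A reader might infer that the window definitely puts exposed patients in the Cohort 1 baseline and dilutes the effect at both ends. The text does not support that: it gives neither lag, and the wait-list end depends on a start date it does not state. A reader might also attach one firm power loss to this point. The early-effect shares above have no source in the documents and serve only to show the range.

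A window centred on the assessment date is also a reasonable way to match service data to the DDCAT. Further, a bias toward zero does not manufacture a benefit for NIATx. Details of the extract are referred to an additional file that is not shown.

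All of this stands as a limit on the claim. It does not remove the gap, because the article states no cut at notification or NIATx start. The calendar also offers little comfort. Recruitment from April 2016 to the end of the Cohort 2 active period in June 2018 is at most 27 months. Two sequential 12-month periods use 24, leaving about 3 months for recruitment, baseline visits and both lags. Lags of 45 days at both ends would use all of that. This assumes the two periods run strictly in sequence, which the missing timeline figure might qualify, and one end alone could still be clean.

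**Conclusion.** The concern holds as a possibility that the plan leaves open. The window can place post-notification admissions in the Cohort 1 pre-implementation cell. If wait-list programs start NIATx within 45 days of their follow-up DDCAT, it can place exposed admissions in the control follow-up cell. Any early benefit then biases the interaction toward zero.

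The loss runs from nil to modest under gradual build-up, and is larger if effects appear early: 0.64 or 0.51 against 0.75 when a quarter of the effect is reached at one or both ends. These figures rest on a back-solved n, a reference proportion of 0.50, even admission over the window and no clustering. It is worth correcting before analysis because the direction is known and the baseline correction is cheap. The documents do not show that the bias is large or that it occurs.

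**What to change.** 1. In both arms, take baseline admissions from the 90 days ending on the baseline DDCAT date. A 45-day baseline would halve that cell.
2. Count baseline services only up to notification, with the same cut-off in both arms.
3. Keep the follow-up window around the post-implementation DDCAT, but exclude wait-list admissions and services after that program's NIATx start.
4. Report the planned two-sided window as a sensitivity analysis, and state the lags from DDCAT to notification and to NIATx start.

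**Cost.** Steps 1 and 2 are date filters on the same state data, with n broadly kept. The baseline and follow-up windows are then no longer placed identically around the DDCAT, though the placement is the same in both arms. Step 3 may lose wait-list follow-up admissions. In the worst case (start on the DDCAT day) that cell halves. With 341.5 in that cell and 683 in the others, SE is about 0.172. Under the linear build-up, power is then Φ(0.3926/0.1718 − 1.96) = 0.63, against 0.70 if the exposed admissions stay in. With a quarter of the effect reached early it is Φ(0.4055/0.1718 − 1.96) = 0.66, against 0.64. Step 3 therefore buys freedom from bias at some cost in precision, and only where the start is prompt.

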### Data collection/variables

The proposed research will explore the impact of the NIATx implementation strategies on positive changes in an implementation fidelity outcome (Aim 1) assessed by the Dual Diagnosis Capability in Addiction Treatment (DDCAT) Index. The DDCAT (Version 4.0) is a 35-item observational benchmark measure of program level dual diagnosis capability. Items are rated on a 5-point scale on degree of integration to generate a total score and scores on seven dimensions [62, 65, 66]. Two studies provide evidence that improvements in or higher DDCAT scores impact patient outcomes. In a study of 185 substance abuse providers, individuals receiving treatment in clinics with higher DDCAT scores had significantly longer length of stay and although not significant, attend four additional treatment sessions [66]. Results from an “open-label” single group repeated measures design (*n* = 8 community addiction treatment agencies) found that overall DDCAT scores increased on average 0.56 points which was associated with corresponding changes in standardized Addiction Severity Index composite severity scores in the psychiatric (μ = 0.034 ± 0.075), alcohol (μ = 0.007 ± 0.120) and drug (μ = 0.014 ± 0.091) problem categories [63]. The DDCAT will be assessed for all participating programs at four distinct time points (Table 2).

**Table 2 Tab2:** Implementation and Fidelity Measures and Frequency of Data Collection

			Data Collection Time Periods			
Aim	Construct	Measure	Baseline	Post-Implementation	Sustainment Period 1	Sustainment Period 2
1	Integrated Services: Fidelity	Dual Diagnosis Capability in Addiction Treatment (DDCAT) Index^1^	X	X	X	X
2	Integrated services: Patients Screened	Proportion of program patients: screened using Gain Short Screener (GSS)	X	X	X	X
2	Integrated Services: Medications	Number of patients receiving a psychotropic or substance use disorder medication	X	X	X	X
2	Integrated Services: Chemical Dependency Services	Number of patients receiving chemical dependency services	X	X	X	X
2	Integrated Services: Mental Health Services	Number of patients receiving mental health services	X	X	X	X
3	Program Facilitators and Barriers to Implementation	Consolidated Framework for Implementation Research (CFIR) Index^1^	X	X	X	X
3	NIATx Stages of Implementation Completion^2^	NIATx strategy fidelity and extent of and duration to complete activities (SIC)		X		

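### Aim 2 calls its pre and post cells independent, but the same programs supply both, and the text does not fix a standard error that allows for this

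*Protocol article*

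**What the plan says.** In Data and power analysis, Specific aim 2, the outcomes are binary at patient level. The article states "This analysis calls for a multi-level logistic regression model". It then says: "The observations at each time point are independent, and therefore this is not a longitudinal (repeated measures) analysis". In its place it describes a 2 by 2 layout: "there are four independent groups (NIATx pre-implementation, NIATx post-implementation, wait-list pre-implementation, and wait-list post-implementation"), "with primary interest in the group by time interaction". At the end of the paragraph it adds: "We will apply a correction to the standard errors to adjust for the interclass correlation at the site level", with the stated purpose of avoiding Type I errors. It names neither the type of correction nor a program-by-period term.

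Two other statements settle who supplies the data. Under Data collection/variables: "The DDCAT will be assessed for all participating programs at four distinct time points". Under Specific aim 2, the patients are "All patients admitted to each program, 45 days before and 45 days after the DDCAT assessment date". Each program therefore contributes one set of patients around its baseline assessment and another around its post-implementation assessment.

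**The concern.** Different patients in the two windows remove dependence at patient level. They do not remove it at program level. There are two sets of programs, each observed twice, not four sets. Screening, diagnosis and referral are largely program practices, so a program's pre and post rates should be correlated, though not perfectly, because practice also drifts.

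The group-by-time effect is a contrast between arms of program-level changes. Its error depends on how strongly a program's rate correlates across periods. An analyst told that the cells are independent and the analysis is not longitudinal has no instruction to link the two periods of a program. Penetration is listed in the Abstract as a primary outcome, so the validity or power of a primary test is at stake.

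The other parts of the plan do recognise the pairing. Aim 1 uses the pre-implementation score as covariate and assumes a pre/post correlation of 0.5. The cost analysis compares pre-post program changes between arms. Only Aim 2 denies it.

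**Working it through.** **The plan's own figure.** The article gives power of 0.75 for OR 1.5 (a 0.10 difference), from standard logistic regression. The effect size is consistent: 0.40 against 0.50 gives (0.50/0.50)/(0.40/0.60) = 1.50. The power cannot be reproduced, because no patient number is given. It can be back-solved. For the interaction log odds ratio with n patients per cell and cell rates 0.50, 0.50, 0.50 and 0.60, n = Σ[1/(p(1−p))] × (1.960 + 0.674)² / (ln 1.5)² = 16.17 × 6.94 / 0.1644 ≈ 683. Over 25 programs that is about 27 per program and period. With rates 0.40, 0.40, 0.40 and 0.50 it is 697, or about 28.

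**Inputs**
- From the article: 25 programs per arm, alpha 0.05 two-sided (both stated for Aim 1: "A two tailed analysis of covariance (α = 0.05) with 25 programs per cohort group"; the alpha is assumed to carry over), unclustered power 0.75.
- Assumed, because the article gives none: m = 27 patients per program and period, ICC ρ = 0.05, between-period correlation of program effects r = 0.8, with r = 0.5 as a variant.

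**Variance factors for the pre-post difference in differences, relative to independent patients**
- Actual: 1 + (m−1)ρ − mρr = 1 + 1.30 − 1.08 = 1.22
- Site random intercept only (linear approximation): 1 − ρr = 0.96
- Design effect on four independent groups: 1 + (m−1)ρ = 2.30

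The intercept-only factor equals the actual one only at r = 1 (both 0.95 here). The independent-groups factor equals it only at r = 0 (both 2.30).

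**Type I error at nominal 0.05**
- Intercept only: 1.96 × √(0.96/1.22) = 1.739, giving 0.082 (simulated 0.078). At r = 0.5 the factors are 1.625 and 0.975, giving 0.129.
- Independent groups: 1.96 × √(2.30/1.22) = 2.691, giving 0.007 (simulated 0.014).
- Standard errors clustered on program across both periods: simulated 0.052.

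**Power, with 0.75 before clustering (standardised effect 1.960 + 0.674 = 2.634)**
- Correct standard error: Φ(2.634/√1.22 − 1.960) = Φ(0.425) ≈ 0.66.
- Independent groups, taking 2.30 as the true variance: Φ(2.634/√2.30 − 1.960) = Φ(−0.223) = 0.41. This is the power such a calculation would report.
- Actual rejection rate if that over-wide standard error is used while the true factor is 1.22: Φ((2.634 − 1.960√2.30)/√1.22) = Φ(−0.306) = 0.38.

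**Range.** Over m 14 to 100, ρ 0.01 to 0.10 and r 0.5 to 0.8, the formulas give a type I error of 0.053 to 0.43 for intercept only, and 0.0001 to 0.043 for independent groups. In simulation (m 27 and 50, ρ 0.05 and 0.10, r 0.5 to 1.0), clustering on program gave 0.042 to 0.059 throughout. The simulated intercept-only test was a linear approximation, not a fitted logistic mixed model.

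**The case against.** The best defence is that the independence sentence is about patients. Different people are admitted in each window, so it is not a patient-level repeated-measures analysis, which is true. The same paragraph commits to a multi-level model and to a site-level correction. If that correction is a cluster-robust variance with the program as cluster over both periods, it allows for pre-post correlation and the interaction standard error is valid. The random-effects structure, variance estimator and degrees of freedom are details that an article may leave to the full protocol or SAP.

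Much of this stands. A reader might infer that the planned standard errors must be wrong. The documents do not support that, because the valid reading is open. A reader might also infer that a standard-error correction on top of a multi-level model is itself a fault. It is not: a program-clustered robust variance guards against a misspecified random-effects structure. Nor does the text show which way any error would go.

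What does not stand is that this is only missing detail. The article goes beyond silence on the dependence structure. It asserts independence of the four cells and draws from it that no repeated-measures structure is needed. That premise is false for the programs, and a SAP written to match would inherit it.

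**Conclusion.** Wrong as written. The four cells are not independent, because each arm's pre and post cells come from the same programs. Whether the resulting test is wrong depends on how the unnamed correction is carried out:
- too liberal under a site random intercept alone, unless the between-period correlation is 1;
- too conservative under a design effect for four independent groups, unless that correlation is 0;
- valid if clustered on program across both periods.

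Under the assumed m = 27, ICC 0.05 and r = 0.8, the cost is a type I error of about 8% in the first case. In the second, power is about 0.4 (0.41 nominal, 0.38 actual) against about 0.66. These figures show that the choice matters. They are not properties of this trial, and smaller ICCs or higher between-period correlations bring the intercept-only error close to 5%. The point needs correcting before analysis but does not show that the planned analysis is invalid.

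**What to change.** Replace the independence statement with one saying that patients differ between windows while programs are measured repeatedly. Then specify one of:
- a multi-level logistic model with a program random intercept and a program-by-period random effect, testing group by time on program-level degrees of freedom. Trial status reports 49 programs randomized, so a plain comparison of program changes between two arms has 49 − 2 = 47;
- standard errors clustered on program across both periods, with a small-sample correction. The correction already promised can stay if it is defined this way.

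A program-level ANCOVA of the post proportion on the pre proportion, in the style of Aim 1, is a valid alternative or sensitivity analysis. It is not equivalent: it conditions on baseline, weights programs differently and estimates a difference in proportions rather than an odds-ratio interaction.

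The cost is a sentence and at most one variance term, with no new data. The downside is a wider confidence interval than an intercept-only model would give when programs drift over time.
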